### Osteopathic manipulative treatment (OMT)

The researcher will perform a standard diagnostic palpatory assessment in order to identify somatic dysfunctions. Somatic dysfunctions are characterized by the functional alteration of the structures of the somatic system, which involve bone, joint, myofascial, vascular, lymphatic, and neural structures. The diagnostic criteria in the evaluation of somatic dysfunctions are expressed in the search (assessment) of asymmetries, changes in range of motion, and abnormalities in the textures of the tissues of the musculoskeletal system. The asymmetries will be evaluated looking for the height of the iliac crests, verification of the curvature of the lumbar spine, and rotation of the femorotibial axes through observation (static inspection) and palpation. Changes in range of motion will be assessed in joints, a group of joints or a region of the system through active and/or passive movement tests. Increased mobility (hypermobility) and decreased mobility (hypomobility) can be found. Abnormalities in tissue texture will be identified by palpatory procedures [17].

Based on the findings of the clinical evaluation, techniques addressing the musculoskeletal systems will be performed at each meeting [18] and/or visceral with direct anatomical correlation with the lumbar [18]. In the musculoskeletal system, the lumbar segment, pelvis, sacrum, and lower limbs will be addressed; these structures are directly connected by the lumbosacral plexus. The techniques used in these segments will be myofascial techniques and joint techniques. Myofascial techniques are techniques directed at the fascia or muscle and through approaches that use continuous palpatory feedback in order to assess and alleviate the somatic dysfunctions involved. Articulation techniques are direct manual techniques that impose movements that can be of low or high speed and low or moderate amplitudes in order to improve joint function. Visceral manipulation will be used in abdominal areas that might be in relationship with the ganglia of the lumbar area, namely renal aortic ganglion (kidneys and gonads), superior mesenteric ganglion (duodenum, jejunum, ileum, cecum, appendix, ascending colon and half of the transverse colon), and inferior mesenteric ganglion (distal part of the transverse colon, descending colon and rectum) [19]. This approach is characterized by manual techniques for diagnosing and treating the viscera and their supporting structures to improve their physiological function [19]. All manual approaches delivered will be recorded in the case report file (CRF).

It is noteworthy that the OMT will be applied only to participants randomly allocated to the intervention group, that is, they will receive OMT in addition to the PNE + CH in the four meetings.

### Sham therapy

The sham therapy will last 30 min. In the first 10 min, the researcher will perform the same evaluation described at OMT section, and in the remaining 20 min, the simulated therapy will be performed. The diagnostic criteria will follow the same steps of the evaluation of somatic dysfunctions, which will be expressed by the assessment of asymmetries, changes in range of motion, and abnormalities in the textures of the tissues of the systems. For the simulated therapy, the researcher will assess the anatomic areas, including the lumbar segment, pelvis, sacrum, and lower limbs, and for simulating the visceral treatment, the researcher will contact the abdominal pelvic quadrants, with superficial touch, without therapeutic intention [20, 21]. For each area, the researcher will mentally count from 120 to 0 to prevent placebo autonomic activation [22]. It is noteworthy that the sham therapy will be applied only to participants randomly allocated to the control group.

### Compliance participation

Participants will be encouraged to bring doubts about the information provided in the previous consultation, and at the beginning of each one, the possibility of doubts regarding the education in neuroscience of pain discussed above will be open. In addition, a review of the topics already discussed will be carried out. Also at that moment, the participants will be asked about the practice of self-hypnosis at home and the other orientations carried out. In this way, we aim to guarantee the participation and adherence of the volunteers in the proposed procedures.

Participants will be asked about the need for co-interventions, such as the use of analgesics or other physical therapies, during the intervals between consultations. All information must be informed to the researchers.

### Multilateral contributions to the development of the protocol

The development of the experimental protocol considered reports and clinical experiences of osteopaths, feedback, and opinions from patients, in addition to a literature review showing the multidimensional approaches.

### Outcomes

Participants will be evaluated by a researcher blind to allocation and the evaluative moments for all outcomes will correspond to the pre-intervention (M0), immediately after the last meeting (M1) and reassessed again in the follow-up of four (M2) weeks after the end of the protocols (Fig. 2).

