#### Secondary outcomes

As secondary outcomes, the patient’s global impression of improvement, central sensitization, and biopsychosocial factors will be evaluated. The patient’s overall impression of improvement will be assessed using the 11-point Improvement Percentage Scale, ranging from − 5, indicating “much worse,” to 0 indicating “no change” to +5 “completely recovered” [23, 27], i.e., higher scores correspond to greater recovery. Central sensitization will be evaluated using the Central Sensitization Questionnaire translated and validated for the Brazilian population [28] composed of two parts (A and B), where part A contains 25 statements, scored on a Likert scale from 0 to 4 points, whose final score can vary from 0 t o100 points, with values closer to 100 indicating a greater degree of central awareness. Part B contains a list of 10 medical diagnoses related to central sensitization syndrome, and the subject is asked about the presence/absence and year of diagnosis. Biopsychosocial factors will be evaluated using the STarT Back Toll questionnaire [29] which classifies the risk of poor prognosis of individuals with LBP in the presence of physical and psychosocial factors and is composed of nine items related to referred pain, dysfunction, comorbidities, and psychosocial factors such as catastrophizing, fear, anxiety, and depression that classify the individual as low, medium, and high risk.

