### Statistical analysis

To analyze the population profile data, we will use the descriptive statistical method and the results will be presented with mean values, medians, standard deviations, minimum and maximum values, and confidence intervals.

Data normality will be determined using the Shapiro-Wilk test, and the comparison of variables between groups at baseline will be performed using Student’s *t*-test for unpaired data for data with normal distribution or the Mann-Whitney test for non-normal data.

Comparisons of primary and secondary outcomes between groups and moments will be performed using the analysis of variance technique for repeated measures model in the two-factor scheme. Repeat measurement data will be checked for sphericity violation using Mauchly’s test, and the Greenhouse-Geisser correction will be used when sphericity is violated.

To analyze the moments, Bonferroni’s post-test for normal distribution or Dunnet’s post-test for non-normal distribution will be used, and the analysis of the different moments between the groups will be carried out using Student’s *t*-test for unpaired data with normal distribution or Mann-Whitney test for non-normal data.

The adopted statistical significance will be set at 5%. Analyses will be performed using the Statistical Package for the Social Sciences software—version 22.0 (SPSS Inc., Chicago, IL, USA) by a researcher blinded to treatments and group allocations using a coded spreadsheet. All the randomized participants will be included in the analysis, in accordance with intention-to-treat principles. To consider all participants, the missing data will be addressed according to the last observation carried forward (M0 or M1) [36]. Analysis and results from this study will be conducted by an independent biostatistician and checked for accuracy.

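### Two analysis rules are wrong as written: a change rating is treated as if it had a baseline value, and a parametric many-to-one test is named for non-normal repeated data

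*Protocol article*

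**What the plan says.** Outcomes sets one schedule without exception: "the evaluative moments for all outcomes will correspond to the pre-intervention (M0"), the end of the last session (M1), and again four weeks after the end of the protocol (M2).

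Secondary outcomes describes the patient's global impression as "assessed using the 11-point Improvement Percentage Scale". It runs from -5 (much worse) "to 0 indicating “no change” to +5 “completely recovered". The same section describes STarT Back as nine items "that classify the individual as low, medium, and high risk".

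Statistical analysis applies one rule to everything: "Comparisons of primary and secondary outcomes between groups and moments will be performed using the analysis of variance technique for repeated measures model", with group and moment as the two factors. It adds a normality check by Shapiro-Wilk, a comparison of the groups at baseline, Mauchly's test with Greenhouse-Geisser correction, and last observation carried forward from M0 or M1. For comparing moments, Bonferroni is named when data are normal; otherwise, "Dunnet’s post-test for non-normal distribution will be used". For comparing groups at each moment, it names the t-test or Mann-Whitney.

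**The concern.** Two written rules do not fit what they are applied to.

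1. **Global improvement.** The scale asks how much the participant has changed. Before treatment there is nothing to rate, yet the schedule, baseline comparison, ANOVA and imputation rule all presuppose an M0 value. The imputation matters most: a zero at M0, carried forward, becomes an outcome for someone who was never assessed after treatment.
2. **Post-test for non-normal data.** Dunnett's test rests on normal theory and compares each level with a single control. It is no remedy for non-normality, and with M0 as control it leaves out M1 against M2. This rule also covers within-group comparisons of pain, pressure threshold and disability, which are the primary outcomes.

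If neither rule is corrected, the analyst has to improvise, and may do so with the data in hand.

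**Working it through.** The plan states no figure on this point, so there is none to reproduce. The check compares the sections and works out what the rules produce.

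**A. Global improvement at M0**

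Inputs: schedule for all outcomes (Outcomes); scale with 0 as no change (Secondary outcomes); ANOVA, baseline test and carry-forward rule (Statistical analysis); 52 participants raised to 60 for losses (Sample size); 1:1 allocation (Study design and participants).

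*If M0 is left blank:* there is no baseline comparison, no complete row for a three-moment ANOVA, and nothing to carry forward for a participant lost before M1.

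*If M0 is set to 0 for everyone:*

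- **Baseline and normality tests.** The M0 variance is 0 in both arms. The t statistic is 0/0, and Shapiro-Wilk on a constant has no meaning.
- **Estimated group effect.** Let d1 and d2 be the arm differences at M1 and M2. Averaged over three moments, the difference is (0 + d1 + d2)/3 = (2/3) × (d1 + d2)/2, two-thirds of the post-treatment average.
- **Group test.** Each participant's mean (0 + a + b)/3 is likewise 2/3 of (a + b)/2. Effect and standard error shrink by the same factor, so F and p are unchanged. In simulation (30 per arm, 4,000 runs, difference 0.65 SD), the group test rejected in 81.8%, 76.7% and 71.4% of runs at assumed M1-M2 correlations of 0.5, 0.7 and 0.9. The rates were the same with and without the M0 column.
- **Sphericity.** With unit variances at M1 and M2 and correlation r, the orthonormal contrasts have variances (1 - r) and (1 + r)/3 and zero covariance. Mauchly's W = (1 - r)(1 + r)/3 ÷ {[(1 - r) + (1 + r)/3]/2}².

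| r | contrast variances | W | Group × moment type I error, uncorrected | Same, Greenhouse-Geisser |
|---|---|---|---|---|
| 0.5 | 0.500, 0.500 | 1.00 | 0.052 | 0.049 |
| 0.7 | 0.300, 0.567 | 0.91 | 0.055 | 0.048 |
| 0.9 | 0.100, 0.633 | 0.47 | 0.076 | 0.053 |

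- **Imputation.** The loss allowance is 60 - 52 = 8 participants. As an upper illustration, suppose all 8 are lost before M1, 4 per arm. Then 8/60 = 13% of the M1 and M2 values would be an assigned 0. If those lost would have resembled the rest of their arm, the arm difference would shrink to 26/30 = 0.87 of its size. The protocol does not say when losses are expected.

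**B. Post-test between moments**

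- Three moments give three pairs: M0-M1, M0-M2 and M1-M2. Dunnett's test against M0 covers two of them.
- Read as Dunn's rank test, the rule would be suited to non-normal data, but the usual form treats samples as independent. Here the same participants supply all three moments.
- The branch would be used. For whole-number 0-10 scores with n = 30, SD 2.0 (from Sample size) and assumed means of 3, 4 and 5, Shapiro-Wilk at 5% rejected in about 40%, 20% and 20% of 3,000 simulated arms per mean. The same normal draws before rounding and truncation rejected in about 5%. This shows how often the non-normal rule would be triggered; it does not measure an error in inference.

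**The case against.** - **The schedule figure is not reproduced, and it may exempt the change scale from M0.** Possible, but the sentence that cites the figure says all outcomes, and the analysis section makes no exception either.
- **A sensible analyst would not enter an M0 value, and the plan already has between-group tests at each moment.** True. Those tests at M1 and M2 are the comparison needed. What remains is that the written ANOVA and the M0 carry-forward say something else.
- **A constant M0 ruins the sphericity test or costs power.** A reader might infer this, and it is wrong. W stays computable, the planned correction holds the interaction error near 5%, and the group test is identical. The two-thirds factor applies to the estimate only.
- **Dunnet is a slip for Dunn.** Plausible, given the spelling and its assignment to non-normal data. The correction may then be mostly one of name, but a version for paired data would still have to be specified.
- **All p-values for non-normal outcomes fail.** A reader might infer this too. The documents do not support it: the post-test only compares moments, and groups are compared by Mann-Whitney.
- **STarT Back classes go into an ANOVA.** Also tempting, but not established. The text describes the instrument's classes much as it does for the Oswestry questionnaire, without saying that the class is the analysed variable. A clarification is enough.

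**Conclusion.** Both rules need correcting. The consequences are limited.

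For global improvement, the rule yields an undefined or constant baseline and baseline checks without a usable result. If M0 is set to 0, the reported three-moment group difference is two-thirds of the post-treatment average, and anyone lost before M1 is entered as unchanged (at most 13% of participants if the whole loss allowance fell before M1). The p-value of the group test is unaffected. This concerns one secondary outcome.

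For the post-test, the named procedure is unsuitable under either reading of the name. It affects within-group comparisons of moments, including those of the primary outcomes. It leaves the between-group comparisons, which carry the primary objective, untouched.

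The conclusion rests on the text applying as written to all outcomes. The simulated figures also rest on the assumed correlations and means shown above.

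**What to change.** 1. In Outcomes and Statistical analysis, exempt global improvement from M0. Compare the arms at M1 and M2 only, leave the scale out of the baseline comparison, and do not carry a value forward from M0.
2. Replace the post-test for non-normal data with a paired rank-based procedure, such as Wilcoxon signed-rank tests on the three pairs of moments with Bonferroni correction (0.05/3 = 0.0167 per pair).
3. Minor: state that STarT Back is analysed by its numeric score. If the three risk classes are analysed, name an ordinal method.

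The cost is a few sentences of wording, with no change to sample size or visits. The change should be fixed before the analyst sees data by group.

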**Methods:**

A randomized controlled clinical trial will be conducted in participants aged 20–60 years with CLBP who will be divided into two groups. Group 1 will receive PNE and CH associated with OMT, and G2 will receive PNE, CH, and sham therapy. In both groups, 4 interventions of a maximum of 50 min and with an interval of 7 days will be performed. As primary outcomes, pain (numerical pain scale), pressure pain threshold (pressure algometer), and disability (Oswestry Disability Questionnaire) will be evaluated and, as a secondary outcome, global impression of improvement (Percent of Improvement Scale), central sensitization (Central Sensitization Questionnaire), biopsychosocial aspects (Start Beck Toll Questionnaire), and behavior of the autonomic nervous system (heart rate variability) will be assessed. Participants will be evaluated in the pre-intervention moments, immediately after the end of the protocol and 4 weeks after the procedures. Randomization will be created through a simple randomized sequence and the evaluator will be blinded to the allocation of intervention groups.

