### Interventions

Participants will be randomly divided into two groups (Fig. 1 and Fig. 2), called PNE + CH + OMT (intervention group) and PNE + CH + sham therapy (control group). For both groups, the participants will be submitted to PNE based on information from the book “Explain Pain” and CH [11, 15]. The intervention group will receive the same approach and additionally four OMT visits and the control group, sham therapy. For both groups, the meetings of OMT or sham therapy will be distributed in 30 min and 20 final minutes with a focus on education with PNE and CH. I All procedures (control and intervention group) will be carried out individually, once a week, with an interval of at least 7 days. Participants who cannot attend on the pre-scheduled days will be offered new dates within the study period, in order to avoid sample loss. All participants will be encouraged to report adverse events at any time to any researcher during the conduction of this study.

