#### Main outcome

Pain and disability will be the main outcomes of the study. Pain will be evaluated through the numerical pain scale, where the participant will be asked about their perception of pain suffered in the last week and will assign a value to it, ranging from 0 to 10, where 0 indicates no pain and 10 indicates worst pain ever felt [11, 23]. Pain will also be assessed by pressure threshold using a pressure algometer device (Fnd-50, PIAB 50-n, Italy) in the lumbar region. The assessment will be conducted specifically on the paraspinal muscles bilaterally at the L1 to L5 levels. Three measurements will be performed at the same point, and the average of the values will be calculated [24]. The distal end of the device will be positioned perpendicularly on the evaluated surface, and constant pressure of 2.55 kg will be applied. Participants will be instructed to indicate the moment when the sensation of pressure changes to a sensation of pain and the value will be recorded. The pain threshold will be defined in kilogram-force (kgf/cm^2^), through the minimum pressure necessary to induce pain in the evaluated region. Still as the main outcome, disability will be evaluated through the Oswestry Disability Questionnaire translated and validated for the Brazilian population [25] composed of ten questions that assess pain intensity and the effect of pain on activities of daily living and classify the individual as minimal (0–20%), moderate (21–40%), severe (41–60%), disability (61–80%), or bed-bound (81–100%) [26].

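### M1 pain recalls the week before session 4, while M1 pressure threshold mixes course and acute effects; LOCF then puts these M1 values in place of missing 4-week results

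*Protocol article*

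**What the plan says.** Under Outcomes, every outcome is assessed before treatment (M0), "immediately after the last meeting (M1") and at M2, four weeks after the end of the protocol. The abstract agrees on the timing: "immediately after the end of the protocol and 4 weeks after the procedures".

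Under Main outcome, pain is rated on a 0 to 10 scale on which "the participant will be asked about their perception of pain suffered in the last week". The same section makes pressure pain threshold, measured on the paraspinal muscles from L1 to L5, part of the main pain outcome. Disability by the Oswestry questionnaire is the other main outcome, and no recall period is stated for it.

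The abstract gives the course as "4 interventions of a maximum of 50 min and with an interval of 7 days will be performed"; Interventions has sessions "once a week, with an interval of at least 7 days". Each session starts with 30 minutes of OMT or sham and ends with 20 minutes of education and hypnosis.

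Under Statistical analysis, "the missing data will be addressed according to the last observation carried forward (M0 or M1").

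**The concern.** A reader will take M1 as the end-of-treatment result. For pain, the outcome on which the sample size rests, the recall question points back to a time when the last session had not yet been given. For pressure threshold the problem runs the other way: a momentary measurement is made soon after hands-on work in the same region. The two primary pain measures could then disagree at M1 merely because they refer to different periods. A short-lived change in threshold could also be read as the effect of the course.

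LOCF adds a second step. For anyone who misses M2, the M1 value is analysed as the 4-week result, although it describes either the week before session 4 (pain) or the minutes after it (threshold).

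**Working it through.** **Recall window for pain.** Inputs: four sessions at least 7 days apart (Interventions), M1 on the day of session 4 (Outcomes), recall of one week (Main outcome).

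- With the shortest spacing, sessions fall on days 0, 7, 14 and 21.
- M1 is on day 21, so its recall window is days 14 to 21. Days after session 4: 0 of 7. Sessions completed before or at the start of the window: 3 of 4.
- With a longer gap g ≥ 7 between sessions 3 and 4, the window starts at (day of session 4 − 7), which is on or after the day of session 3. The result is the same.
- M2 is on day 21 + 28 = 49, with recall window days 42 to 49. All 7 days follow session 4, and the window opens 42 − 21 = 21 days after it.

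**Pressure threshold and HRV.** These are momentary, so no recall window applies. At M1 all four sessions have been given, and a session of up to 50 minutes has just ended. The OMT section describes myofascial and joint techniques to the lumbar segment, among other regions. The Sham therapy section describes superficial touch. The threshold site lies within that region, so the arms differ in local mechanical input shortly before measurement. M0 precedes any session, so the change from M0 to M1 contains both a course effect and an acute effect, and the planned data cannot separate them. Hypnosis, which in session 4 includes deep relaxation, is common to both arms. For HRV, Secondary outcomes refers to a baseline and a closing recording without saying whether the latter is M1 or M2.

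**Size of the LOCF effect on pain.** Planned loss allowance (Sample size): 52 × 1.15 = 59.8, rounded to 60, which reproduces the stated total. The planning difference is 1.3 points. Whether 52 itself follows from the stated inputs is a separate matter and is not needed here.

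Let L be the share of M2 values carried from M1, equal in both arms, and k the M1 difference as a fraction of the M2 difference. The analysed M2 difference is then

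1.3 × [(1 − L) + L × k].

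The documents give no value for k. As assumed ranges:

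| L | k | Analysed difference |
|---|---|---|
| 0.05 | 0.75 | 1.3 × 0.9875 = 1.28 |
| 0.05 | 0.50 | 1.3 × 0.975 = 1.27 |
| 0.15 | 0.75 | 1.3 × 0.9625 = 1.25 |
| 0.15 | 0.50 | 1.3 × 0.925 = 1.20 |
| 0.15 | 0 | 1.3 × 0.85 = 1.11 |

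The last row is a limiting case. It also covers participants with neither M1 nor M2, whose M0 value is carried and whose expected difference between arms is zero under randomisation.

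**The case against.** The best defence is that the design already contains the assessment that is wanted. M2 covers every outcome, its recall week lies wholly after the course, and observed M2 values are untouched by LOCF. The background states a hypothesis for both the short and the medium term, so an immediate visit is deliberate and is described as such. Timing is identical in the two arms, and the sham takes the same 30 minutes with hands-on contact. All of this stands. It confines the point to what M1 measures and how M1 values are used.

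Four stronger readings are tempting, and the documents do not support them.

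- A reader might infer that no primary outcome at M1 gives the effect of the full course. Threshold is measured after all four sessions and does include it, mixed with an acute response. For Oswestry no recall period is stated, so nothing can be said.
- A reader might scale the 1.3 points by the share of sessions received and quote a loss of power at M1. Nothing says how much session 4 adds. The 1.3 points come from an earlier trial whose assessment timing is not shown; if it used the same recall at the end of treatment, the figure already contains any dilution.
- A reader might infer that LOCF creates a sustained pain effect. If M1 pain is diluted, carrying it forward understates the M2 difference. Overstatement is conceivable for threshold, but its size cannot be derived.
- A reader might infer bias between arms. Identical timing rules that out as a consequence of this point alone.

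Fig. 2, which sets out the schedule, is not shown and could define the M1 day differently. The text of Outcomes and of the abstract is nevertheless explicit and consistent.

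**Conclusion.** The point holds in a limited form. On the stated timings, M1 pain covers none of the time after session 4 and at most three completed sessions. This follows from the calendar and assumes only that participants answer the recall question as asked and that M1 is on the day of session 4. M1 threshold, and HRV if its closing recording is M1, reflects the completed course plus an acute response that cannot be removed. What changes is the meaning of the M1 results.

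The LOCF consequence is secondary. At a carried share of up to 15%, equal in both arms, the pain difference at M2 falls from 1.3 to no less than about 1.1 points even if M1 held none of the effect, and to 1.20 to 1.28 over the middle of the assumed range. The direction rests on k being below 1; if the effect fades by M2, k could exceed 1 and LOCF would inflate the difference. Unequal loss between arms is not covered by this calculation.

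**What to change.** 1. Under Statistical analysis, replace LOCF with a likelihood-based repeated-measures model for each continuous outcome, with arm, visit and their interaction, using all observed M0, M1 and M2 data. M1 values then inform the estimate at M2 through their correlation with it, but are not entered as 4-week results. The model assumes that data are missing at random given what was observed.
2. Base the claim about the completed course on the M2 contrast, since M2 is the only assessment whose pain recall week follows all four sessions.
3. Report M1 pain as the week before session 4, and M1 threshold as an immediate post-session response. State which visit supplies the closing HRV recording; if it is M1, label it in the same way.

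Cost: no extra visit or measurement. Items 1 and 3 are changes to analysis and reporting text. Naming M2 as the primary time point is more than wording: recruitment is already under way (Trial status), so it needs notification to the ethics committee and a registry update (Protocol amendments), made before results are seen. The main answer would then rest on the visit where more loss to follow-up is to be expected, and the short-term part of the hypothesis becomes supportive.
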